3. STUDY DESIGN
   1. Study Design Description

This is a phase III multicentre, randomised, double-blind, placebo-controlled, parallel-group study.

The study will be conducted in the Russian Federation and the Republic of Belarus at about 10 trial sites. Accrual will be competitive.

The purpose of the study is the evaluation of the efficacy, reactogenicity and safety of the Ad5-nCoV vaccine compared with placebo in adults aged 18 to 85 years.

Five hundred (500) volunteers will be randomised in two treatment (vaccination) groups in a 3:1 ratio (Ad5-nCoV:Placebo) as follows:

- Group 1: a single dose of the Ad5-nCoV vaccine.
- Group 2: a single dose of placebo.

The study design includes 7 outpatient visits to trial sites and 5 phone calls with the study doctor:

- Screening visit (Day −10...Day −1).
- Visit 1 (Day 0) — randomisation, a single administration of the investigational product, volunteer’s stay at the trial site for 2 hours after vaccination, a phone call with the study doctor in 5–8 hours after vaccination.
- Visit 2 (Day 2) — reactogenicity and safety evaluation in 48–72 hours after vaccination.
- Visit 3 (Day 7) — reactogenicity and safety evaluation in 7 days after vaccination.
- Visit 4 (Day 14) — safety and immunogenicity evaluation in 14 days after vaccination.
- Visit 5 (Day 28) — safety and immunogenicity evaluation in 28 days after vaccination.
- Phone calls with the study doctor in 2, 3, 4 and 5 months after vaccination (safety evaluation).
- Visit 6 (Month 6) — safety and immunogenicity evaluation in 6 months after vaccination.

During each next visit and phone call after vaccination, subjects will be interviewed regarding the signs of acute respiratory viral infection to detect and confirm a COVID-19 case (exploratory protective efficacy evaluation).

The investigation of the cellular immune response will be performed in a separate cohort of at least 60 subjects randomised at trial sites in Moscow.

The study flowchart is shown in Figure 9.

Schedule of procedures is presented in Table 14. A detailed description of the study plan is presented in section 6.

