One interim and one final analysis are planned for the study. The unblinded interim analysis will be performed after obtaining efficacy, reactogenicity and safety data through Visit 5 (Day 28) for the first 200 volunteers randomised in the study. Based on the results of this analysis, an interim clinical trial report will be prepared, which will be submitted to regulatory authorities to make a decision on the registration of the Ad5-nCoV vaccine.

The final clinical trial report will be prepared after obtaining all data for all volunteers randomised in the study, i.e. after the completion of the final visit by all the volunteers in 6 months after vaccination. The final clinical trial report will be also submitted to regulatory authorities.

Screening Vaccination Follow-up period

| **Ad5-nCoV** |
| --- |
| **Placebo** |
|  |

| **Randomisation**  **Single vaccination** |
| --- |

| Day −10–−1 | Day 0 | Day 2 | Day 7 | Day 14 | Day 28 | Month 2, 3, 4, 5 | Month 6 |
| --- | --- | --- | --- | --- | --- | --- | --- |
| **Visit 0** | **Visit 1** | **Visit 2** | **Visit 3** | **Visit 4** | **Visit 5** | **Phone call** | **Visit 6** |

____________________________________

Reactogenicity evaluation

__________________________________________________________________________________________

Efficacy and safety evaluation

Figure 9 Study Flowchart

*Visit 1 includes volunteer’s stay at the trial site for 2 hours after vaccination and phone call with the study doctor in 5–8 hours after vaccination

- 1. Measures Taken to Minimise/Avoid Bias

To minimise bias, randomisation and blinding will be used for the study.

1. Randomisation

At Visit 1 (Day 0), screened and eligible volunteers will be randomly allocated into the Ad5-nCoV group or the placebo group in a 3:1 ratio (Ad5-nCoV:placebo).

The randomisation plan with randomisation numbers for the subjects will be provided by an independent statistician using a validated system including a pseudorandom number generator with a seed value. Thus, the resulted randomisation sequence with numbers and prescribed products will be both reproducible and non-predictable. Block randomisation and stratification by the trial site will be used in this study.

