1. DATA MANAGEMENT AND STATISTICAL ANALYSIS
   1. Sample Size Calculation and Justification

To determine the number of subjects required to test the hypothesis relating to the primary variable (proportion of subjects with seroconversion on Day 28 after vaccination), the following conservative assumptions are used:

- study power is about 90 %
- two-sided significance level (alpha) is 5 %; Pocock’s corrected alpha level for multiple comparisons of the primary variable due to an interim analysis is 0.02616 and 0.03039 for the interim and final analysis (performed after obtaining primary variable data for all randomised subjects), respectively
- proportion of subjects with seroconversion in the placebo group is 20 %
- proposed difference between the placebo and vaccine group in terms of the primary variable is 30–60 % (odds ratio is 4–16)
- randomisation ratio between the vaccine and placebo group is 3:1, respectively
- two countries (accrual will be competitive, so a uniform assignment is considered for the calculation)
- dropout from the study/statistical analysis during the observation period of 28 days is about 10 %.

According to the results of the sample size calculation performed using the PASS 12 software (Professional License, NCSS LLC (www.ncss.com)), 180 subjects should be included in the statistical analysis to ensure the power of 90 % for the between-group comparison of the primary variable considering the assumption of 20 % seroconversion rate in the placebo group and the superiority of the vaccine group of at least 30 % (conservative assumption, odds ratio = 4), as well as the corrected two-sided significance level of 0.02616 (one-sided level of 0.01308) and randomisation ratio of 3:1. The number of subjects corresponding to the conservative estimate of differences between the vaccine and placebo groups in terms of the primary variable is chosen to ensure the provision of safety data. Considering the possible dropout from the study/statistical analysis during the observation period of 28 days (10 % of subjects), the number of randomised subjects should be increased up to 200 (in a 3:1 ratio).

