To compare the seroconversion rate (including the primary efficacy endpoint) by evaluation time points, a statistical hypothesis of the statistical superiority of the vaccine against placebo will be tested:

Н_0_: OR = 1 Н_A_: OR > 1

OR = odds ratio: OR = [P_1_/(1-P_1_)] / [P_2_/(1-P_2_)]

P_1_ and P_2_ — proportion of subjects with seroconversion in the vaccine and placebo group, respectively.

The results will be descriptively provided by trial sites and countries. The primary variable will be analysed using the Mantel-Haenszel test with the country as a factor if at the time of the analysis the analysis set in each country will have a proper number of subjects with the assessed primary endpoint (at least 20 % of the planned number of subjects for the interim analysis in the vaccine and placebo groups). Otherwise, data will be analysed using the trial site as a factor. Detailed information about combining data for small trial sites will be presented in the statistical analysis plan. Hypothesis testing will be carried out using the *X* test (or Fisher’s exact test). Corrected and uncorrected two-sided confidence intervals for the percentage differences will be also presented.

Additionally, between-group comparisons will be also performed using logistic regression with the treatment group as a fixed factor, the country as a factor and pre-existing antibody titer as a covariate. Pre-existing anti-Ad5 neutralising antibody titers (low and negative (≤ 200) vs high (> 200)), sex and age will be also considered as potential model factors. Odds ratios will be presented with appropriate 95 % confidence intervals.

Similarly, the proportion of subjects with cellular immune response will be analysed.

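### Randomisation is stratified by trial site, but the primary test defaults to country and may use different factors at the interim and final analyses

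*Protocol*

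**What the plan says.** On randomisation, protocol section 5.2 says: "Block randomisation and stratification by the trial site will be used in this study". Section 5.1 gives the scale: "The study will be conducted in the Russian Federation and the Republic of Belarus at about 10 trial sites". Accrual is competitive.

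For the primary endpoint, section 9.2 (Efficacy Analysis) takes country as the first choice: "The primary variable will be analysed using the Mantel-Haenszel test with the country as a factor if at the time of the analysis" each country has enough subjects with the endpoint assessed. Enough means "at least 20 % of the planned number of subjects for the interim analysis in the vaccine and placebo groups". If that fails: "Otherwise, data will be analysed using the trial site as a factor". On pooling it adds: "Detailed information about combining data for small trial sites will be presented in the statistical analysis plan". The following sentence says that hypotheses are tested with a test whose name survives in the text only as X, or with Fisher's exact test. It does not say how either relates to the Mantel-Haenszel test.

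The sample size in section 9.1 is for a Cochran/Mantel-Haenszel test with two country strata: "two countries (accrual will be competitive, so a uniform assignment is considered for the calculation". It uses the "corrected two-sided significance level of 0.02616 (one-sided level of 0.01308) and randomisation ratio of 3:1". Under section 9.3 the interim results go to regulators for the registration decision, and the trial continues to a final analysis.

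**The concern.** Two features of the rule are unsatisfactory.

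First, the default analysis drops the factor used to randomise, and no reason is given. Blocks within sites keep between-site variation out of the treatment difference. A country-stratified test still counts that variation in its variance, so it is too cautious when sites within a country differ. Section 3.3.2.2 reports that pre-existing Ad5 immunity and age affected the antibody response in phase II, and both could vary by site.

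Second, the threshold is a fixed number of subjects, while the number assessed grows from the interim to the final analysis. The smaller country can miss it at the first look and pass it at the second. The p-value sent to regulators would then come from a different test than the final one. The unexplained mention of Fisher's exact test adds to the doubt about which p-value decides.

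**Working it through.** **1. The plan's own figures.** Inputs from section 9.1: placebo 20 %, vaccine 50 % (odds ratio 4), one-sided alpha 0.01308 (z = 2.224), power 90 % (z = 1.282), vaccine share s = 0.75, two identical strata.

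- Pooled rate: 0.75 × 0.50 + 0.25 × 0.20 = 0.425
- D = s(1 − s)(p1 − p2) = 0.1875 × 0.30 = 0.05625
- V0 = 0.1875 × 0.425 × 0.575 = 0.04582
- V1 = 0.1875 × (0.25 × 0.50 × 0.50 + 0.75 × 0.20 × 0.80) = 0.03422
- N = (2.224 √V0 + 1.282 √V1)² / D² = 160.7
- With continuity correction: (N/4)(1 + √(1 + 2/(D·N)))² = 178.045

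This is the stated 178.045. The other four rows of the table also reproduce. Dropout: 180/0.9 = 200. Pocock spending at 0.4: 0.05 × ln(1 + (e − 1) × 0.4) = 0.02616. The final level comes to 0.03038 against the stated 0.03039. No figure is wrong, and the calculation fits the country default.

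**2. When the factor changes.** The planned interim number is 200, split 150 and 50. Twenty per cent is 30 vaccine and 10 placebo subjects per country if read per arm, or 40 per country if read as a total. With 10 % dropout, about 180 subjects are evaluable at the interim and 450 at the final analysis.

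- Share needed at the interim: 40/180 = 22 %
- Share needed at the final analysis: 40/450 = 9 %

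If the smaller country supplies between about 9 % and 22 % of subjects, the interim uses site and the final uses country. Counts only grow, so the change goes one way. Competitive accrual leaves the split uncontrolled.

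**3. What the factor costs.** The protocol gives no between-site variation, site sizes or block size. Assumed: 10 equal sites, 7 in one country and 3 in the other, blocks of 4, and normal site effects on the logit scale with SD 0 to 1.5. Simulation used 60,000 runs per setting, without continuity correction.

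| Between-site SD | 0 | 0.5 | 1.0 | 1.5 |
|---|---|---|---|---|
| Power, N = 180, odds ratio 4: country | 93.2 % | 91.3 % | 84.3 % | 73.0 % |
| Power, same: site | 93.1 % | 91.9 % | 88.5 % | 83.6 % |
| Null, N = 200, rate 20 %, nominal 0.0131: country | 0.0099 | 0.0092 | 0.0071 | 0.0052 |
| Null, same: site | 0.0104 | 0.0104 | 0.0115 | 0.0117 |
| Null, N = 500, rate 50 %, nominal 0.0152: country | 0.0150 | 0.0137 | 0.0099 | 0.0068 |
| Null, same: site | 0.0150 | 0.0154 | 0.0157 | 0.0154 |

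The power gap is 0, about 1, 4 and 11 points. With the continuity correction that underlies N = 178, country gives 90.3, 87.7, 79.2 and 65.7 % and site 90.2, 88.7, 84.1 and 77.7 %, so the gap is 0, 1, 5 and 12 points. The simulation error of the N = 500 null rates is about √(0.0152 × 0.985/60,000) = 0.0005, so the site values there do not differ from nominal.

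**4. Phase II response rates.** With vaccine at 97 % (section 3.3.2.2) and placebo at an assumed 2 % (phase II saw no rise), both tests have power of about 100 % at N = 200 for SD 0, 1.0 and 1.5.

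**The case against.** The strongest reply is that the rule is pre-specified. It names a default, a numeric trigger and a fallback, and the trigger counts assessed subjects without regard to outcome. The default matches the two country strata of the sample size. This stands: a reader might infer that the test is left open until the data are seen, and the protocol does not support that. What is loose is the wording of the threshold and its use at each look.

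A reader might also infer that several candidate tests threaten the alpha of 0.02616 and 0.03039. They do not in any material way. Taking the better of the country and site tests gave at most about 0.012 against 0.0131 at N = 200. In a separate run of 100,000, taking the smallest p-value of the country, site, chi-square and Fisher tests gave at most 0.0158 against 0.0152 at N = 500, and that high only with no site effect at a 50 % rate.

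It is tempting to read the X test as an unstratified chi-square competing with the primary test. The symbol is damaged, the Mantel-Haenszel statistic is itself referred to a chi-square distribution, and the paragraph covers all seroconversion endpoints. Only the undefined role of Fisher's test remains.

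Nor is the fallback plainly backwards. When one country is tiny, moving to site returns to the randomisation factor, and pooling of small sites properly belongs in the SAP. But if site strata are acceptable then, they are acceptable from the start.

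Finally, site differences may be small: subjects are seronegative at entry and one central laboratory runs the assay. That is fair, and it limits the size of the point.

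**Conclusion.** The point holds as a modest improvement to the primary analysis. The default factor is not the randomisation factor, the factor can differ between the two looks, the threshold has two readings, and the place of Fisher's exact test is unstated.

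The country test should not be called conservative without qualification. It is so only if sites differ within a country; with no such difference the two tests perform alike. The loss of about 1, 4 to 5 and 11 points of power at SD 0.5, 1.0 and 1.5 rests on assumed site variation, ten equal sites and the plan's odds ratio of 4. With an effect near that seen in phase II, neither the interim nor the final conclusion would change. The sample size and both alpha levels stand.

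**What to change.** In section 9.2 (Efficacy Analysis), name one primary test for both looks: Mantel-Haenszel stratified by randomisation site, with sites below a stated size pooled within their country. Sites are nested in countries, so site strata also absorb country differences. The pooling rule can sit in the SAP, but should be fixed before the interim unblinding; section 9.2 now requires the SAP only before the database lock.

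Delete the accrual-dependent switch. Label the country-stratified test and Fisher's exact test as sensitivity analyses. If the sponsor prefers country, it should give the reason and keep that factor at both looks.

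The cost is a few sentences, with no added subjects or data.

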Blood samples were taken on Day 0 immediately after vaccination, on Day 14 and on Day 28 after vaccination to measure the specific antibody titer against the receptor-binding domain (RBD) using ELISA. The limit of detection of specific antibodies against the RBD using ELISA was 1:40. Neutralising antibody titer against live SARS-CoV-2 (SARS-CoV-2/human/CHN/Wuhan_IME-BJ01/2020, GenBank No. MT291831.1) or pseudovirus (spike glycoprotein-expressing pseudovirus system based on the vesicular stomatitis virus) and cellular immune response before vaccination and in 28 days after vaccination were also measured. Limits of detection of neutralising antibodies against live SARS-CoV-2 and pseudovirus were 1:8 and 1:10, respectively. If antibodies were undetectable, a half LoD value was used for calculations. Cellular immune response (IFN-γ expression) stimulated by the pool of spike glycoprotein was evaluated using ELISpot. Positive IFN-γ ELISpot response was defined as ≥ 5 spot-forming cells per 1х10^5^ peripheral blood mononuclear cells and at least two-fold increase of this parameter compared to the baseline. Titers of neutralising antibodies against the Ad5 vector of the test vaccine were measured by a serum neutralisation test.

Humoral Immunity Assessment Results

The results are shown in Figure 8 below. On Day 28 after vaccination, the seroconversion rate (at least four-fold increase in antibody titer compared to the baseline) was 96 % (95 % CI 93–98) in the 10х10^10^ VP group [seroconversion was detected in 244 of 253 volunteers], 97 % (95 % CI 92–99) in the 5х10^10^ VP group [seroconversion was detected in 125 of 126 volunteers], and no antibody titer increase was observed in the placebo group. RBD-specific antibody titer on Day 28 was 656.5 (575.2–749.2) in the 10х10^10^ VP group and 571.0 (467.6–697.3) in the 5х10^10^ VP group.

The seroconversion rate of neutralising antibodies against live SARS-CoV-2 was 59 % (95 % CI 52–65) in the 10х10^10^ VP group and 47 % (95 % CI 39–56) in the 5х10^10^ VP group. No significant differences between the two dose groups in the seroconversion rate of neutralising antibodies against live virus and pseudovirus were observed.

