A detailed description of statistical methods will be provided in the Statistical Analysis Plan before the database lock. General information on the proposed statistical analysis is provided below.

Descriptive statistics will be provided for all demographic and other baseline characteristics, immunogenicity, cellular immune response, efficacy and safety parameters, as well as their changes (if applicable) during the study by evaluation time points and treatment groups. Demographic characteristics and efficacy endpoints will also be presented by the pre-existing anti-Ad5 neutralising antibody titers (low and negative (≤ 1:200) vs high (> 1:200)). Descriptive statistics for quantitative parameters will include the mean, the standard deviation (SD), the median, the first and third quartiles, the minimum and maximum values and the number of valid observations. The geometric mean values will be also presented for antibody titres and fold-rises in titers. Qualitative data will be presented as rates and percentage. Where applicable, 95 % confidence intervals will also be provided.

For undetermined values of the geometric mean titer, geometric mean fold-rise and seroconversion rate, the following algorithm will be used: 1) if the antibody titer is below the lower limit of quantitation, a half LoD value will be used 2) if the antibody titer is above the maximum limit of quantitation, the maximum dilution will be used.

Missing Data

Only available values will be used for statistical analysis. Missing values will not be imputed.

Procedures for Reporting Any Deviations from the Original Statistical Plan

In the case of any deviations from the planned statistical analysis described in the protocol, the clinical trial report will include the description and justification of implemented changes.

- - 1. Efficacy Analysis

The primary variable will be analysed during the interim and final analysis using the corrected significance level (overall significance level is two-sided 5 %). Secondary variables will be analysed using the two-sided 5 % significance level.

Efficacy variables representing the seroconversion rate (proportion of subjects with at least four-times increase in antibody titers), including the primary efficacy endpoint, will be presented by evaluation time points and treatment groups.

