Efficacy variable (antibody geometric mean titer (GMT) and neutralising antibody GMT) will be presented and compared by evaluation time points based on the calculated 95 % confidence interval using ANOVA/ANCOVA following the logarithmic transformation of base 10. The ANCOVA model will include the treatment group as a fixed factor, country/trial site as a factor and pre-existing (log-transformed) antibody titer as a covariate. Pre-existing anti-Ad5 neutralising antibody titers (low and negative (≤ 200) vs high (> 200)^1^), sex and age will be also considered as potential model factors. Mean log-transformed differences between the study groups (vaccine/placebo) will be evaluated with the corresponding 95 % confidence interval. The point estimates of the mean differences and the corresponding confidence intervals will be back-transformed.

Efficacy variable (geometric mean fold-rise in antibody titers and neutralising antibody titers) for each treatment group and each antibody GMT evaluation time point will be assessed with the corresponding two-sided 95 % CIs following log-transformation (log10), point estimation of the difference and confidence intervals, and back-transformation of obtained values. Between-group comparisons will be performed using ANOVA/ANCOVA following the logarithmic transformation of base 10. The ANCOVA model will include the treatment group as a fixed factor, country/trial site as a factor and pre-existing (log-transformed) antibody titer as a covariate. Pre-existing anti-Ad5 neutralising antibody titers (low and negative (≤ 200) vs high (> 200)^[[7]](#footnote-7)^), sex and age will be also considered as potential model factors.

Exploratory efficacy endpoints (frequency of confirmed COVID-19 cases during 6 months after vaccination, frequency of confirmed COVID-19 cases requiring hospitalisation, frequency of severe COVID-19 cases, and frequency of lethal COVID-19 cases (except for the cases occurred during the first 14 days after vaccination)) will be presented descriptively by treatment groups. Kaplan-Meier survival estimates will be also presented if applicable.

1. Safety Analysis

The safety analysis will be performed in the safety analysis set using descriptive methods.

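### ANOVA/ANCOVA on log10 titres assumes equal variances in arms expected to differ and allocated 3:1, so the precision reported for the SARS-CoV-2 GMTs and for the vaccine/placebo GMT and fold-rise ratios can be wrong in either direction

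*Protocol*

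**What the plan says.** Section 9.2.3 (Efficacy Analysis) sets the method for titres. GMTs "will be presented and compared by evaluation time points based on the calculated 95 % confidence interval using ANOVA/ANCOVA following the logarithmic transformation", with treatment group, country or site, and log baseline titre as model terms. "Mean log-transformed differences between the study groups (vaccine/placebo) will be evaluated with the corresponding 95 % confidence interval", and the result is back-transformed to a ratio.

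Fold-rise is handled in two steps. Each arm's fold-rise "for each treatment group and each antibody GMT evaluation time point will be assessed with the corresponding two-sided 95 % CIs following log-transformation (log10"), without reference to a model. Then: "Between-group comparisons will be performed using ANOVA/ANCOVA following the logarithmic transformation of base 10".

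Section 9.2.2 gives the floor rule: "if the antibody titer is below the lower limit of quantitation, a half LoD value will be used". Section 9.2.3 also states: "Secondary variables will be analysed using the two-sided 5 % significance level". Section 5.1 sets the allocation: "Five hundred (500) volunteers will be randomised in two treatment (vaccination) groups in a 3:1 ratio (Ad5-nCoV:Placebo"). Nothing in section 9 mentions unequal variances, and the terms pooled or common variance do not appear.

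**The concern.** Ordinary ANOVA/ANCOVA estimates one residual variance for both arms. That matters little when the arms are of equal size or equally variable. Here neither is expected.

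Subjects must be antibody-negative at screening (Inclusion Criteria, section 5.4), low titres are replaced by a single value, and in phase II "no antibody titer increase was observed in the placebo group" on Day 28 (section 3.3.2.2). Placebo RBD titres may therefore be close to constant, while vaccine titres spread widely. Pooling assigns vaccine-arm variance to the small placebo arm, where it is divided by only 125, and dilutes it in the vaccine arm.

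At stake are the intervals printed beside the GMTs and the GMT and fold-rise ratios, including those at the 200-subject interim, whose report goes to regulators for the registration decision.

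**Working it through.** The protocol states no planned width for any GMT interval, so there is no figure of its own to reproduce. The check is for RBD on Day 28.

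**Inputs**
- Allocation: 500 at 3:1, so n1 = 375 and n2 = 125 (section 5.1).
- Phase II RBD GMT at 5x10^10 VP: 571.0, 95 % CI 467.6–697.3 (section 3.3.2.2), n = 129 (Table 12).
- Phase II RBD LoD 1:40, so half LoD = 20 (section 3.3.2.2).
- Placebo seroconversion assumed for planning: 20 % (section 9.1).

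**Vaccine SD.** Half-width = log10(697.3/467.6)/2 = 0.0868. Dividing by t(128) = 1.979 gives SE 0.0439; times √129 gives s1 = 0.498, s1² = 0.248.

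**Limit case, every placebo titre at half LoD (s2 = 0)**
- Pooled variance = (374 × 0.248 + 124 × 0)/498 = 0.186, SD 0.432.
- Pooled SE of the log10 difference = √[0.186 × (1/375 + 1/125)] = 0.0446.
- Separate-variance SE = √(0.248/375) = 0.0257.
- Factor = 0.0446/0.0257 = 1.73, which is √3.
- Ratio 571/20 = 28.6: CI 23.3–34.9 pooled, 25.4–32.1 separate.
- Vaccine GMT: CI 516–632 with the pooled SD, 508–642 with its own. The width on the log scale is 0.432/0.498 = 0.87 of what it should be; coverage 2Φ(1.96 × 0.87) − 1 ≈ 91 %.

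**General form.** At exactly 3:1 and large n, factor² = (3s1² + s2²)/(s1² + 3s2²). Pooling in effect swaps the weights of the two arms. The factor is 1 only when s1 = s2.

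**Placebo responders.** Suppose a share p of placebo subjects has vaccine-like titres (mean shift d = log10 28.55 = 1.456, SD 0.498) and the rest are at the floor. Then s2² = p × 0.248 + p(1 − p) × d². If responders rise exactly four-fold instead, s2² = p(1 − p) × (log10 4)².

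For p = 0.20, vaccine-like: s2² = 0.0496 + 0.16 × 2.119 = 0.389. Pooled variance = (374 × 0.248 + 124 × 0.389)/498 = 0.283. Pooled SE 0.055, separate SE √(0.248/375 + 0.389/125) = 0.061, factor 0.89.

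| Placebo arm (assumed) | s2 | Ratio CI width, pooled/separate | Ratio CI coverage | Vaccine GMT CI width, pooled/own | Vaccine GMT CI coverage |
|---|---|---|---|---|---|
| all at half LoD | 0 | 1.73 | 99.9 % | 0.87 | 91 % |
| 2 % vaccine-like | 0.216 | 1.43 | 99.5 % | 0.89 | 92 % |
| 5 % vaccine-like | 0.336 | 1.21 | 98 % | 0.93 | 93 % |
| 10 % vaccine-like | 0.464 | 1.03 | 96 % | 0.98 | 95 % |
| 20 % vaccine-like | 0.623 | 0.89 | 92 % | 1.07 | 96 % |
| 20 % exactly four-fold | 0.241 | 1.38 | 99 % | 0.90 | 92 % |

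At the interim (150 and 50) the limit-case factor is again 1.73. The calculation leaves out covariates. With seronegative entry the baseline SARS-CoV-2 titre should itself be near the floor, so adjusting for it cannot be relied on to even out the variances.

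**The case against.** The strongest reply is that the protocol never says the variance is pooled. Section 9.2.2 calls this text general information and leaves detailed methods to the SAP, which could specify unequal variances. It stands that pooling is inferred from the model's name. But the protocol does name the model for these intervals, one residual variance is what that name ordinarily means, and section 9.2.2 requires departures from the protocol's planned analysis to be described and justified in the report. Proposing a better method differs from complaining of missing detail.

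Other parts of the reply stand and limit the point:
- A reader might infer that each arm's fold-rise interval is affected. Section 9.2.3 describes those intervals separately and brings in ANOVA/ANCOVA only for the between-group comparison.
- A reader might infer that the ratio interval is too wide in every comparison. The flat placebo arm is documented for RBD on Day 28 in one earlier trial. It cannot be carried over to Month 6 during community transmission, and the protocol's own 20 % planning value can reverse the direction.
- The floor argument does not reach anti-Ad5 titres: about half of the phase II subjects were above 1:200 before vaccination (Table 12).
- The vaccine GMT interval is too narrow only if it is taken from the model and not from the arm's own data.
- These endpoints are secondary, and a ratio near 29 excludes 1 under either method.

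**Conclusion.** The point holds as a matter of reported precision. With 3:1 allocation and unequal variances, an ordinary ANOVA/ANCOVA interval is right only by coincidence, when the two SDs happen to agree. For RBD on Day 28 the ratio interval is up to 1.73 times too wide and a model-based vaccine GMT interval about 13 % too narrow; with 20 % placebo seroconversion the ratio factor is about 0.89 to 1.38, depending on how high the responders' titres are. The too-narrow intervals are the anticonservative part.

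This rests on three assumptions: the ordinary equal-variance form of the model, a vaccine-arm SD like that of phase II, and the placebo scenarios in the table. It does not support doubt about the primary seroconversion test, the conclusion of superiority, the anti-Ad5 titres or the per-group fold-rise intervals.

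**What to change.** In section 9.2.3, or in the SAP before the unblinded interim analysis, keep the log10 model and its terms but state that between-group GMT and fold-rise contrasts use heteroscedasticity-consistent (HC3) or Welch-type standard errors, and that each arm's GMT interval is computed from that arm's own SD. These choices allow for unequal variances in every scenario in the table, so nobody has to guess the placebo infection rate.

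Do not do this through a likelihood model with a separate residual variance per arm. If placebo titres are constant, the likelihood is unbounded as that variance goes to zero, and near that limit the flat arm dictates the shared covariate slopes.

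The cost is a sentence or two of specification. No change to data collection, sample size or the primary analysis is needed.
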